# A feasibility hybrid II randomised controlled trial of volunteer ‘Health Champions’ supporting people with serious mental illness manage their physical health: study protocol

**DOI:** 10.1186/s40814-021-00854-8

**Published:** 2021-05-31

**Keywords:** Serious mental illness, Physical health, Intervention, Volunteers

## Abstract

**Background:**

People with serious mental illnesses (SMI) such as schizophrenia often also have physical health illnesses and interventions are needed to address the resultant multimorbidity and reduced life expectancy. Research has shown that volunteers can support people with SMI. This protocol describes a feasibility randomised controlled trial (RCT) of a novel intervention involving volunteer ‘Health Champions’ supporting people with SMI to manage and improve their physical health.

**Methods:**

This is a feasibility hybrid II randomised effectiveness-implementation controlled trial. The intervention involves training volunteers to be ‘Health Champions’ to support individual people with SMI using mental health services. This face-to-face or remote support will take place weekly and last for up to 9 months following initial introduction. This study will recruit 120 participants to compare Health Champions to treatment as usual for people with SMI using secondary community mental health services in South London, UK. We will measure the clinical and cost effectiveness including quality of life. We will measure the implementation outcomes of acceptability, feasibility, appropriateness, fidelity, barriers and enablers, unintended consequences, adoption and sustainability.

**Discussion:**

There is a need for interventions to support people with SMI with their physical health. If this feasibility trial is successful, a definitive trial will follow to fully evaluate the clinical, cost and implementation effectiveness of Health Champions supporting people with SMI.

**Trial registration:**

ClinicalTrials.gov, registration no: NCT04124744.

## Background

People diagnosed with a serious mental illness (SMI) such as schizophrenia, bipolar disorder and major depression have poorer physical health and experience more multimorbidity than the general population [1–3]. People with SMI have higher rates of cardiovascular disease [4], diabetes [5] and respiratory disease [6]. Recent research has shown that this health gap is widening [2].

The reasons for this inequality are complex, encompassing individual, health service and societal factors [7]. Individual level factors include severity of illness and symptoms which can affect how people access help. The health service factors include fragmentation of physical and mental health services, the impact of cuts in services, and ‘diagnostic overshadowing’ where physical health symptoms are seen as part of mental illness by health professionals. Social factors include stigma, poverty, poor housing [7] and social isolation [8]. There is a clear need for interventions that promote the physical health of this population at all of these levels [9]. Solutions need to be flexible enough to meet the needs of individual service users and this can be difficult in England within over-stretched primary care and mental health services [10].

There is little evidence on how best to support people with SMI to manage their physical health. A Cochrane review of physical health advice for service users with SMI demonstrated a modest improvement in quality of life [11]. However, the review also highlighted a significant research gap in assessing physical health advice interventions and their impact on service users’ physical health. This research gap was also found in a recent systematic review of physical health screening in this population [12]. A recently published Lancet Psychiatry Commission summarises the best available evidence for interventions targeting specific health outcomes such as smoking and obesity and advocates community-based interventions [13].

In this protocol, we describe a novel intervention in which volunteers will work alongside people using community mental health services for up to 9 months to support them with managing their physical health. There is emerging literature on the benefits of mental health service users being supported by volunteers both for the service user and volunteer. For service users, this includes contact with someone non-judgemental who helps facilitate increased social interaction, and for volunteers, the feeling they are giving something back and helping others [14–16]. However, there is little evidence regarding volunteers working with service users specifically on their physical health. This study aims to contribute to this much needed area by evaluating the introduction of volunteer ‘Health Champions’ who are matched with service users to support them in the community in setting and working towards their own defined physical health goals as part of a randomised controlled trial.

The aims of this study are to evaluate the feasibility of deploying trained volunteer ‘Health Champions’ to support people with SMI in managing their physical health, compared to treatment as usual. We aim to collect clinical, economic and implementation measures to assess the feasibility and to understand the implementation challenges of undertaking the intervention in routine practice.

As the study will start during the COVID-19 pandemic, contacts will be face-to-face or remote, in line with contemporaneous national and local guidance and approvals.

### Development of the intervention

#### Phase 1 (February 2018-January 2019): Initial conceptualisation

The intervention was developed as part of a larger ‘Integrated Mental and Physical Health Systems’ (IMPHS) Programme funded by the Maudsley Charity and involving SLaM service users and providers. The initial conceptualisation of the intervention came from discussion between the Maudsley Charity, the SLaM Volunteer Manager and the IMPHS project scientists. SLaM volunteers already support people in a variety of ways including befriending and the scope to use volunteers to support physical health was developed into an idea for an intervention. Advice was sought from the King’s Health Partners (KHP) Mind and Body Programme Expert Advisory Group and the SLaM Serious Mental Illness Service User Group as part of the initial development of the Health Champions project.

#### Phase 2 (February-October 2019): Development of a theory of change

Initial conceptualisation of the intervention was followed by development of a Theory of Change (ToC) for the study. A draft ToC was produced by the IMPHS project team, which was subsequently reviewed and refined in two stakeholder workshops (on 30 September and 1 October 2019) with 22 participants. ToC workshop participants were service users, carers, clinical staff, voluntary sector representatives and volunteers.

The ToC that emerged from this process (see Table 1) proposes that, by working with a Health Champion, participants will improve their own self-management of their physical health by goal-setting and problem-solving with their Health Champion. This may lead to improvement in their physical and mental health and a decrease in their treatment burden. All of these will then lead to improved physical and mental quality of life. The ToC also proposes a possible decrease in loneliness both for the duration of the intervention and afterwards.

**Table 1 Tab1:** Theory of change-modified items from Stakeholder Workshops in bold

Inputs/resources	Facilitators/barriers	Actions/activities	Outcomes	Impacts
Project staff SLaM volunteer manager Health Champions Volunteer Coordinator **Service user and carer steering group** Volunteers SLaM staff and infrastructure **Participants** **Carers** Local community organisations e.g.: tba Training and supervision for health champions **Small amount of funding for activities during the intervention**	Facilitators: Large number of existing volunteers within SLaM Knowledge and experience of project team Support from SLaM **Skills and experience of Health Champions** Barriers: Ability to recruit enough health champions New role—needs to be clearly explained **Poverty and housing issues for participants**	Recruit Health Champions **Recruit participants and ensure they have full details of the intervention** **Training of Health Champions including on how to build relationships and coaching skills** **Support and supervision for Health Champions during the intervention** **Effective matching of Health Champions and participants** Mapping of voluntary and community sector organisations Role of Health Champions **Help to set goals** • To give light-touch education and information to patients to promote healthy lifestyles Specific activities for patient-Health Champion pairs to do together may include: • Encouraging participation and engagement in healthy hobbies and activities in the community—for instance, swimming, walking, use of gyms/exercise facilities (e.g. park gyms, and local authority sports centres) • Taking part in group activities and exercise—building social networks, self-esteem and confidence • Providing tips and guidance around nutrition, healthy cooking and eating (including food shopping and food traffic light systems), and cooking together • Helping patients attend follow up GP or outpatient appointments for physical health issues **Groups for Health Champions only and Health Champions and participants to meet and discuss intervention/progress/share ideas** **Possible teaching sessions for Health Champions and participants on areas of interest**	For participants Increased confidence in dealing with physical health including ability to attend physical health appointments Increased knowledge of how to deal with physical health concerns and problems Increase in doing things to improve physical health-e.g. being more physically active, change in diet **Increase in enjoyable activities** Reduced levels of social isolation Increase in level of health screenings **Improved mental health** **For Health Champions** **Improved health** **Learning new skills** **Ability to give back** **For SLaM services** **Support with the participants they work with** **Better knowledge of local community organisations**	Improved quality of life Improved physical health of patients Improved patient experience and engagement Improved links with the voluntary and community sector to address physical and mental health Increased awareness and understanding amongst volunteers, patients and carers of physical health and its interaction with mental health, and how to promote healthy lifestyles Increased awareness and understanding of the types of services (and who would most benefit) provided by the voluntary and community sector

#### Phase 3 (March 2019-December 2019): Operationalisation of the intervention

Whilst the ToC was being developed and consulted on, we finessed and operationalised the intervention. This included developing the processes for recruiting and training the volunteers to deliver the intervention (see Section 2.7.1 for details), and for recruiting people with SMI as participants into the trial (see Section 2.8).

### Feasibility outcomes

We will measure the following feasibility outcomes:
Feasibility of the intervention measured using the Feasibility of Intervention Measure [17] and qualitative interviews with participants and Health Champions.Appropriateness of the intervention to both participants and Health Champions measured using the Intervention Appropriateness Measure [17] and qualitative interviews with participants and Health Champions.Fidelity to the intervention which we will measure using a content analysis of Health Champions and participants journals to assess fidelity of the delivery of the intervention and fidelity of receipt of the intervention, supervision records, and the number and percentage of meetings between each Health Champion and participant.Barriers and facilitators and unintended consequences will be measured using qualitative interviews with a subset of 30% participants and Health Champions chosen at random after the intervention recording whether the intervention was delivered face to face or remotely plus details from the journals and supervision records. We will also interview all participants who drop out of the intervention to understand their reasons for this.Adoption of the intervention will be measured by the number and percentage of participants that start the intervention, how many sessions they have and how long (in months) they stay in the intervention.Adoption and sustainability will also be assessed using interviews with SLaM managers and commissioners.

## Methods and analysis

### Design

This is a feasibility hybrid II effectiveness-implementation randomised controlled trial. Hybrid type II trials [18] are at the cutting edge of applied health research and are used to jointly assess the clinical effectiveness and implementation strategies of evidence-based interventions so that findings can be interpreted in the light of how best to implement such interventions at scale and with sustainability, including economic viability. The schedule of enrolment, interventions and assessments is shown in Table 2.

**Table 2 Tab2:** Data collection plan

	Baseline assessment	Follow-up assessment 1 (at end of intervention or after 9 months)	Follow-up assessment 2 (6 months after end of intervention or 9 month assessment)

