### The intervention

#### Overview of the intervention

We will recruit and train volunteers to act as Health Champions. These Health Champions will support individual service users to set and work towards their own individually decided physical health goals. They will meet face-to-face once a week for up to 9 months at a location decided by the participant and in line with their goals or remotely depending on the guidance on social distancing at the time. If the participant reaches their goals within 9 months, they can choose to end their involvement. The Health Champions will be supported by a Volunteer Coordinator who will be based in the SLaM Volunteer team and will be recruited specifically for this role.

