### Participant recruitment

We will recruit participants from CMHTs across all four South London boroughs that are covered by SLaM services—namely the boroughs of Lambeth, Lewisham, Southwark and Croydon. Participants will be recruited using two methods.
Directly recruited from the community teams by staff identifying and recruiting people who are eligible for the study. Staff will be made aware of the eligibility criteria of the study.Using the SLaM Consent for Contact (C4C) service to identify people using CMHTs who have already consented to be approached by researchers to take part in research projects.

Once potential participants have been identified, they will be contacted by a researcher who will explain the purpose and nature of the study to them. If they are interested in taking part, a researcher will meet with them and give them the patient information sheet to read and answer any questions. If possible these meetings will be face-to-face, if not they will be by telephone or on Microsoft Teams. If they are still interested in taking part, they will complete a written consent form. If the meeting is not face-to-face, consent forms can either be posted to the participant or they can complete an online consent form. A baseline assessment will then be done which will also be either face-to-face or remotely. After this assessment, they will be allocated to either the intervention or control group (see “Randomisation” section for details below).

Participants in the intervention group will then follow the intervention as outlined above. Participants in the control group will receive a copy of a workbook on managing physical health and a ‘Participant Physical Health Journal’. Both groups will be asked to complete follow-up assessments at 9 months and 15 months after baseline. All participants will be reimbursed £10 for each assessment, £30 in total.

If any participants lose mental capacity during the trial, they will be withdrawn from the study.

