## Data collection

### Aim 1: Clinical effectiveness of the intervention

#### Primary outcome

Our primary outcome is physical health-related quality of life which we will measure using the EQ-5D-5L [21] at baseline, at the end of the intervention (nine months after baseline) and 6 months after the end of the intervention.

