#### Secondary outcomes

The following outcomes will be measured at baseline, and at the end of the intervention (9 months after baseline) and 6 after the end of the intervention.
Self-management using the 10-item Patient Activation Measure [22].Mental Health related Quality of Life using the 10-item Recovering Quality of Life (ReQoL) measure [23].Treatment burden using the 10-item Multimorbidity Treatment Burden Questionnaire [24].Loneliness using the 6-item De Jong Gierveld Loneliness Scale [25].We will record participant’s use of physical health services and physical health screenings.We will record demographic information including age, gender, ethnicity, educational level, living arrangements, employment status and relationship status.

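### The protocol gives conflicting follow-up schedules, and one of them would let assessment timing depend on trial arm and on reaching goals

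*Protocol article*

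**What the plan says.** The Design section introduces Table 2 as the schedule: "The schedule of enrolment, interventions and assessments is shown in Table 2". Its two follow-up columns are headed "Follow-up assessment 1 (at end of intervention or after 9 months" and "Follow-up assessment 2 (6 months after end of intervention or 9 month assessment". Neither heading says which option applies to which arm, or from what date the 9 months run.

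Participant recruitment gives a different rule: "Both groups will be asked to complete follow-up assessments at 9 months and 15 months after baseline".

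Under Aim 1, Primary outcome, the EQ-5D-5L is taken at baseline, then "at the end of the intervention (nine months after baseline) and 6 months after the end of the intervention". Secondary outcomes makes the same equation: "at the end of the intervention (9 months after baseline".

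Two statements about the intervention bear on this. Overview of the intervention says: "If the participant reaches their goals within 9 months, they can choose to end their involvement". The Abstract (Methods) says the support will "last for up to 9 months following initial introduction", so its clock starts at introduction to the Health Champion, not at baseline.

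The Quantitative data section labels the repeated measures in the primary model as one taken after the intervention and one at 9 months. It later speaks of a post-intervention score and a 9-month follow-up score.

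**The concern.** Only the intervention arm has an intervention that can end. If the end of the intervention is a valid anchor for assessment, visit timing in that arm depends on an event after randomisation, namely reaching one's goals, while controls can only be seen at 9 and 15 months. The EQ-5D-5L, the primary clinical outcome, would then be compared between arms at different times, with the timing in one arm tied to how well the participant is doing.

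The same applies to the other outcomes in both follow-up columns of Table 2. The EQ-5D-5L also feeds the QALY estimates, and the Health Questionnaire asks about service use over the preceding 6 months, so the periods those data cover would differ between arms too. Once visits have been held at different times, this cannot be undone.

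**Working it through.** **Reproducing the stated schedule.** Let m be the month after baseline at which the intervention ends. The end-of-intervention option in Table 2 gives follow-up 1 = m and follow-up 2 = m + 6. With m = 9 this gives 9 and 15 months, which matches Participant recruitment. The two rules coincide only at m = 9.

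**Early finishers (m below 9).** The gap from controls is 9 − m at both follow-ups.

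| m | Follow-up 1 | Follow-up 2 | Ahead of controls (9 and 15) |
|---|---|---|---|
| 3 | 3 | 9 | 6 months |
| 6 | 6 | 12 | 3 months |
| 8 | 8 | 14 | 1 month |

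**Arm means.** The protocol gives no share of early finishers, so the share p is an assumption. Mean follow-up 1 = 9 − p(9 − m) and mean follow-up 2 = 15 − p(9 − m).

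- p = 10% (6 of 60), m = 6: 9 − 0.1 × 3 = 8.7 and 15 − 0.3 = 14.7 months.
- p = 50% (30 of 60), m = 3: 9 − 0.5 × 6 = 6.0 and 15 − 3 = 12.0 months.

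**Periods covered.** At m = 3, observation from baseline lasts 9 months against 15. The 6-month service-use recall at follow-up 1 would run from 3 − 6 = −3 to 3 months, half of it before baseline. For controls it runs from 3 to 9 months.

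**Late starters.** If introduction comes w months after baseline and a full course follows, the intervention ends at 9 + w. The protocol gives no figure for w. Assuming w = 1 to 3, the end falls at 10 to 12 months and the visit six months later at 16 to 18. The phrase in the outcome sections equating the end of the intervention with nine months after baseline would then fail in the other direction.

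**Model labels.** If the 9-month label means nine months after baseline, it duplicates the post-intervention visit and leaves month 15 out. If it means nine months after the end of the intervention, it falls at 9 + 9 = 18 months. Neither reading gives 9 and 15.

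**With one clock.** If both arms are assessed at 9 and 15 months after baseline, the timing difference is 0 at both visits for every m and w.

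**The case against.** The strongest reply is that the right rule is already printed. Participant recruitment fixes both groups, not only controls, and both outcome sections gloss the end of the intervention as nine months after baseline. Table 2 itself offers a 9-month option. The early-stopping sentence concerns involvement in the intervention and does not say that the assessment moves with it. All of this stands. A reader might infer that the plan is to measure the arms at different times; the documents do not support that. They leave it possible without settling it.

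A reader might also infer that the bias would favour the intervention, because early finishers would be seen just as they succeed. That is not shown: earlier assessment also leaves less time for quality of life to change. Nor can a QALY bias be put in figures. That would require assumed stopping times, shares and utilities, and raw QALY totals summed to each person's last visit. The economic section describes decision modelling with evidence synthesis and no such sum.

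Finally, this is a feasibility study, mainly descriptive and not powered for effectiveness. That limits the harm but does not remove it, since the protocol intends to use any observed EQ-5D-5L change to guide a larger trial. Nor is this the compression of a journal article: the printed statements conflict with one another.

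The late-start point is weaker than the rest. No gap between baseline and introduction is stated, and under the rule in Participant recruitment such a gap would not make visit times differ between arms.

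**Conclusion.** The concern holds as an internal contradiction. Table 2, Participant recruitment, the two outcome sections and the model description do not give one schedule. The end of the intervention is not nine months after baseline for anyone who stops early, and may not be for anyone introduced to a Health Champion well after baseline.

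If Table 2 is followed literally, between-arm outcomes could be taken 1 to 6 months early for intervention participants who finish between months 8 and 3. Under the assumed shares and stopping months, the arm mean moves by 0.3 to 3.0 months at each follow-up. That could bias the between-arm comparison, in an unknown direction, and make QALY and service-use periods unequal. If the recruitment rule is followed, none of this arises. The sample size is unaffected.

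**What to change.** Take the rule in Participant recruitment as the single schedule and bring the other places into line:

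- **Table 2:** head the follow-up columns as 9 months and 15 months after baseline, for both arms, whenever the intervention starts or ends.
- **Primary outcome and Secondary outcomes:** state the same two times and remove the equation with the end of the intervention. The Secondary outcomes sentence also lacks the unit after its 6.
- **Quantitative data:** relabel the model timepoints as 9 and 15 months after baseline.
- **Intervention dates:** record start and stop dates as separate variables.
- **End-of-intervention contact:** if one is wanted, use it only for the implementation measures (acceptability, appropriateness, feasibility and the related interviews).

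No new time origin is needed: baseline is already common to both arms, and allocation follows the baseline assessment. The cost is a few lines of rewording and two recorded dates, with no extra required visits. The downside is that the EQ-5D-5L is not captured at the moment an early finisher stops.
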